# Multiarm, non-randomised, single-centre feasibility study—investigation of the differential biology between benign and malignant renal masses using advanced magnetic resonance imaging techniques (IBM-Renal): protocol

**DOI:** 10.1136/bmjopen-2024-083980

**Published:** 2024-10-26

**Keywords:** Kidney tumours, Magnetic resonance imaging, Functional Magnetic Resonance Imaging

## Abstract

**Introduction:**

Localised renal masses are an increasing burden on healthcare due to the rising number of cases. However, conventional imaging cannot reliably distinguish between benign and malignant renal masses, and renal mass biopsies are unable to characterise the entirety of the tumour due to sampling error, which may lead to delayed treatment or overtreatment. There is an unmet clinical need to develop novel imaging techniques to characterise renal masses more accurately. Renal tumours demonstrate characteristic metabolic reprogramming, and novel MRI methods have the potential to detect these metabolic perturbations, which may therefore aid accurate characterisation. Here, we present our study protocol for the investigation of the differential biology of benign and malignant renal masses using advanced MRI techniques (IBM-Renal).

**Methods and analysis:**

IBM-Renal is a multiarm, single-centre, non-randomised, feasibility study with the aim to provide preliminary evidence for the potential role of the novel MRI techniques to phenotype localised renal lesions. 30 patients with localised renal masses will be recruited to three imaging arms, with 10 patients in each: (1) hyperpolarised [1-^13^C]-pyruvate MRI, (2) deuterium metabolic imaging (DMI) and (3) sodium MRI. The diagnosis will be made on samples acquired at biopsy or at surgery. The primary objective is the technical development of the novel MRI techniques, with the ultimate aim to understand whether these can identify differences between benign and malignant tumours, while the secondary objectives aim to assess how complementary the techniques are, and if they provide additional information. The exploratory objective is to link imaging findings with clinical data and molecular analyses for the biological validation of the novel MRI techniques.

**Ethics and dissemination:**

This study was ethically approved (UK REC HRA: 22/EE/0136; current protocol version 2.1 dated 11 August 2022). The plans for dissemination include presentations at conferences, publications in scientific journals, a doctoral thesis and patient and public involvement.

**Trial registration number:**

NCT06016075.NCT06016075

STRENGTHS AND LIMITATIONS OF THIS STUDYThis is the first prospective study to investigate the role of deuterium metabolic imaging and sodium MRI for the characterisation of indeterminate renal masses.A patient can be recruited into different imaging arms of the study, thus allowing for direct comparison of novel MRI techniques for informing about the nature of the renal masses.Multimodal assessment of these renal masses, including clinical, imaging and pathology data, will be conducted.Limitations of the study include potential pathological undergrading of benign renal masses, as some of these diagnoses are based on a single biopsy.If the primary outcomes are met, this will be used to inform a large-scale study.

## Introduction

### Clinical need in management of localised renal masses

 The incidence of renal cancer has increased significantly during the last two decades, with 13 322 new cases diagnosed annually in the UK, corresponding to an age-standardised incidence of 8.2 per 100 000.^1^ Depending on histological subtype and other tumour-related and patient-related factors (such as tumour location, complexity, patient comorbidities, surgical history, renal function), the management options range from active surveillance to radical surgical resection.^2^ An important unmet clinical need is that conventional imaging methods cannot reliably distinguish aggressive renal cell carcinoma (RCC) subtypes from indolent renal masses.^3^ Although an invasive renal mass biopsy is a key tool for distinguishing radiologically indeterminate renal lesions, it is subject to sampling error, which is particularly problematic in heterogeneous lesions. Biopsies may also be clinically challenging to perform and are non-diagnostic in up to 20% of cases, which can result in either unnecessary or delayed surgery.^4^,^7^ Importantly, earlier detection and treatment have not resulted in decreased mortality, suggesting that there is an overdiagnosis and potentially overtreatment of benign renal tumours.^1 8^ As RCC remains one of the most lethal urological malignancies,^9^ there is a pressing need for novel methods to identify and characterise renal masses more accurately.^10^

### Metabolic changes in RCC

Renal cell tumours harbour significant metabolic perturbations and different histologic subtypes have distinct metabolic phenotypes. In clear cell RCC (ccRCC), the major genetic driver is the loss of the von Hippel-Lindau tumour suppressor gene, which leads to accumulation of hypoxia-inducible factor 1α with downstream transcriptional activation of pathways involved in glycolysis.^11 12^ Metabolomic analyses have confirmed increased lactate labelling after [U-^13^C]glucose infusion in ccRCC tumours compared with adjacent normal kidney with glycolysis increasing in a grade-dependent manner.^13^,^15^ On the other hand, renal oncocytomas, which are classified as benign renal masses, suppress oxidative metabolism due to defective complex I within the mitochondrial electron transport chain.^1116^,^18^ Therefore, it is not clear to what extent the ratio between glycolytic and oxidative metabolism varies across aggressiveness of renal neoplasms.^17 19^ Recently, studies have also reported mitochondrial respiration defects in both renal oncocytoma and its malignant counterpart, chromophobe RCC (chRCC), with the potential for differentiation based on genomic, transcriptomic and metabolic levels.^16 17 20^ The question to be addressed in this study is whether MRI can be used to phenotype the aggressiveness of renal masses, and can therefore implement to help risk-stratify tumours to inform management decisions.

### Imaging metabolism

Building on the evidence described above, we hypothesise that novel MRI techniques can non-invasively characterise whole-tumour metabolism and its heterogeneity across renal tumours. The most common clinical tool for assessment of tumour metabolism uses a radiolabelled glucose analogue, in conjunction with positron emission tomography, but its effectiveness is limited by renal excretion of the tracer, and it has failed to show success in characterising renal tumours.^21 22^
^99m^Tc-sestamibi in conjunction with single-photon emission CT has been used to detect a variable degree of tracer uptake in renal oncocytoma compared with chRCC in a small number of patients, which has been attributed to the tracer accumulation in cells with high levels of mitochondria.^23 24^ However, both techniques expose patients to ionising radiation, offer poor soft tissue contrast and the inability to detect specific downstream metabolites or their metabolic compartmentalisation.^25 26^

Our multidisciplinary group are developing novel non-radioactive and non-invasive clinical tools for imaging tumour metabolism. For example, hyperpolarised [1-^13^C]-pyruvate MRI (HP ^13^C-MRI), following injection of intravenous hyperpolarised ^13^C-pyruvate, can be used to simultaneously detect glycolytic metabolism in the cytosol and oxidative metabolism in the mitochondria in tissue where there is sufficient metabolism.^27^ Two recent papers have shown that ^13^C-lactate labelling can be used to distinguish high-grade ccRCC from lower-grade tumours, driven by the pyruvate transporter (monocarboxylate transporter 1; MCT1).^28^ Furthermore, a case of a renal oncocytoma displayed the lowest pyruvate-to-lactate conversion compared with a range of malignant masses, including ccRCCs, suggesting that this may be a tool for discriminating these lesions.^28^

More recently, we have implemented deuterium (^2^H) metabolic imaging (DMI) at clinical field strength as an alternative method for non-invasive detection of metabolism using orally administered deuterated glucose.^29^ This method can also be used to detect cytosolic lactate formation and mitochondrial oxidative metabolism, and is complementary to the information provided by HP ^13^C-MRI.^30 31^ We have undertaken this in the brain at clinical field strength (3T) and will apply it to the kidney in this study using dedicated hardware to assess whether differential glucose metabolism can be used to differentiate benign from malignant lesions.

### Imaging cellularity and structure

To complement the metabolic measurements, we will evaluate non-invasive methods to distinguish benign from malignant lesions based on differences in cellularity on histology. Sodium MRI (^23^Na-MRI) is a complementary tool to probe tissue structure as a measure of the tissue sodium concentration, which is a function of cellularity due to the concentration gradient across the cell membrane. The method can also be used to extract an intracellular-weighted component of the sodium pool as a measure of the transmembrane sodium gradient.^32^ In the presence of hypoxia, the sodium/potassium ATP pump may be inhibited, leading to alterations in the sodium concentration.^32 33^ We have previously shown how ^23^Na-MRI can be used to demonstrate the Na^+^ gradient across the corticomedullary axis in the normal kidney and how this can be used to assess dynamic changes in renal sodium.^33^ We have also recently developed a novel birdcage MRI coil system for high resolution ^23^Na-MRI of the normal kidneys,^34^ which we will apply to imaging focal renal pathology as part of this study. We have shown the potential of ^23^Na-MRI in several cancer types, correlating with cellularity on histology, and will apply this to small renal masses for the first time here.^35 36^

In addition, we have developed complementary ^1^H-MRI methods to quantitatively map T2 relaxation properties within tissue for assessment of diffuse renal disease.^37^ Here, we will assess whether these can distinguish benign from malignant lesions. These parameters are dependent on the local tissue chemical properties and reflect the microenvironmental differences between benign and malignant disease.

### Rationale for the study

This feasibility study will explore the role of multimodal MRI in characterising localised renal masses and how it can exploit the known biological differences between benign and malignant lesions. The project will assess if MRI can probe structure, function and metabolism within the tumour and its microenvironment using three techniques:

HP ^13^C-MRI as a non-invasive measure of tissue metabolism following injection of hyperpolarised ^13^C-pyruvate to probe tumour lactate labelling.DMI as an alternative method to probe both glycolytic and oxidative metabolism following oral ^2^H-labelled glucose to detect both lactate and the combined signal from glutamine+glutamate.Measures of the tumour cellularity, heterogeneity and membrane ion gradients using ^23^Na-MRI and fast, high-resolution measures of T2 relaxation.

The aim is to provide preliminary evidence for the potential role of these techniques to phenotype localised renal lesions and how they can be used as part of a larger multicentre study. The ultimate goal is to provide non-invasive tools for early detection of small, aggressive renal tumours to enable timely surgical intervention.

## Methods and analysis

The study is reported in accordance to Standard Protocol Items: Recommendations for Interventional Trials (SPIRIT) checklist,^38^ with SPIRIT-Path extension.^39^

### Study design and objectives

The investigation of differential biology of benign and malignant renal masses using advanced MRI techniques study is designed as a feasibility study to acquire preliminary data with set imaging protocols as defined based on our previous work, and these results will be used to optimise future imaging protocols and to inform large-scale studies. The study will be conducted as a non-randomised, physiological imaging study in patients with localised renal masses, at a single site: Addenbrooke’s Hospital, Cambridge University Hospitals NHS Foundation Trust. For all imaging studies, the primary objective will be the technical development of each imaging technique with ultimate aim to understand whether the methods can identify any differences between benign and malignant tumours, including measuring the ^13^C-pyruvate-to-lactate conversion with HP ^13^C-MRI, quantifying sodium concentration using ^23^Na-MRI, detecting ^2^H-glucose and its metabolites using DMI. Secondary objectives will aim to compare the imaging techniques to understand if they can produce complementary information. As an exploratory part of the study, the objective will be to link the imaging data with clinical data and tissue molecular analyses for biological validation of the novel MRI techniques. Diagnostic accuracy analysis is not foreseen at this stage.

### Participant selection

Participants will be identified through multidisciplinary team meetings or by clinical teams involved in their routine care at Addenbrooke’s Hospital, and recruited if they meet all the inclusion and none of the exclusion criteria as detailed in table 1. The participants will be allocated into three imaging arms with 10 patients in each: (1) HP ^13^C-MRI; (2) DMI; and (3) ^23^Na-MRI. ^1^H-MRI with T2-mapping will be performed in all patients. The recruited participant will be allocated to one of these imaging techniques by the chief investigator. This will be based on the availability of kits for HP ^13^C-MRI, availability of the deuterated glucose drink for the DMI study and/or availability of the research MRI scanner. The aim is to recruit at least four patients in each arm with an oncocytic renal neoplasm (mostly oncocytomas) and at least four patients with RCCs as determined by clinical pathology assessment to enable direct comparison. Half of the patients in each arm will be selected from a cohort of newly diagnosed renal masses and imaged prior to biopsy, with 75%–80% of these expected to have RCCs, and most of the remainder having oncocytic neoplasms. The other half will be acquired from retrospective cohorts of patients with previously diagnosed oncocytic neoplasms on active surveillance at least 6 weeks post biopsy. Diagnosis will be made on tissue samples acquired at biopsy or at surgery if applicable, using molecular markers where possible. This approach will ensure an appropriate balance between benign and malignant lesions in each cohort.

**Table 1 T1:** Inclusion and exclusion criteria for selection of study participants

Inclusion criteria	Exclusion criteria
Over 18 years old. Able to and provide written informed consent to participate. If female: postmenopausal or if a woman of childbearing potential using a suitable contraception. If male, using a suitable contraceptive method for the duration of the study. Radiologically suspected or pathologically confirmed benign or malignant renal masses, as determined by standard clinical practice. Capable of undergoing a minimum of one study visit.	The presence of any of the following will preclude participation, as determined by the delegated investigator: Contraindication or inability to tolerate MRI. Pregnant or actively breastfeeding woman. If using an intrauterine contraceptive device as a method of contraception, the device should be MRI safe at 3 T (researcher to confirm). Clinically significant cardiac, pulmonary or neurological diseases as determined by the investigators. Laboratory abnormalities that may impact on the study results. Any other significant medical or psychiatric history rendering the subject ineligible as deemed by the investigators.

Participants may be removed from the study at their choice or at the investigator’s discretion if it is felt to be clinically appropriate. Reasons for participant withdrawal will be recorded. Primary reasons for withdrawal may include serious adverse event (SAE), withdrawal of consent, lost to follow-up, participant non-compliance, or study closed or terminated. Participants who are withdrawn from the study or do not complete at least one scan will be replaced.

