### The sample size calculation and outcomes

The study has been powered to assess changes in the ^13^C-pyruvate metabolism from the data we collected from nine treatment-naïve renal tumour patients.^28^ This work showed that the median pyruvate-to-lactate conversion constant (*k*_PL_) in ccRCCs was 0.0065 (range 0.0024–0.0151), while it was 0.0043 (range 0.0028–0.0076) in the normal kidney. This study also reported metabolism in a single case of renal oncocytoma, which showed both the lowest conversion constant and lactate-to-pyruvate ratio (LAC/PYR). There are currently no published studies assessing DMI and ^23^Na-MRI quantitative parameters in human kidney tumours.

Based on the parameters obtained from the HP-^13^C-MRI, pragmatic sample sizes have been determined for priming of the study: we plan to include up to 30 participants in total: 15 with benign renal masses and 15 with malignant renal masses. These participants will be divided equally into three imaging arms (HP ^13^C-MRI, ^23^Na-MRI and DMI); therefore five benign and five malignant participants will be recruited to each imaging arm. If participants are willing to take part in the optional additional scan using a different imaging technique, these participants will be counted towards both arms of the study and therefore the total number recruited to the study will be less than 30 participants. The planned timeline for the study is as follows: start date on 1 January 2023, primary completion date on 31 August 2025, with study completion by 1 January 2026.

Descriptive statistics will be used. The primary covariates to be studied are as follows:

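### The recruitment scheme is expected to give 3.75 to 4 RCCs per arm, not the five malignant cases stated, and misses the plan's aim of at least four RCCs in 26% to 37% of arms

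*Protocol article*

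**What the plan says.** Under Participant selection, the protocol article fixes how each arm is filled:

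- Size: "The participants will be allocated into three imaging arms with 10 patients in each".
- First source: "Half of the patients in each arm will be selected from a cohort of newly diagnosed renal masses". These patients are "imaged prior to biopsy, with 75%–80% of these expected to have RCCs, and most of the remainder having oncocytic neoplasms".
- Second source: "The other half will be acquired from retrospective cohorts of patients with previously diagnosed oncocytic neoplasms on active surveillance".
- Aim: "The aim is to recruit at least four patients in each arm with an oncocytic renal neoplasm (mostly oncocytomas) and at least four patients" with RCC. The RCC part reads "at least four patients with RCCs as determined by clinical pathology assessment to enable direct comparison".

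The section closes by asserting that this scheme secures a suitable benign-malignant balance in every cohort.

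Under The sample size calculation and outcomes, up to 30 participants are planned, 15 benign and 15 malignant, divided equally over the arms: "therefore five benign and five malignant participants will be recruited to each imaging arm". The same section calls the sizes pragmatic and the analysis descriptive.

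**The concern.** The five surveillance patients in an arm already carry an oncocytic diagnosis, so the scheme counts on no RCC from them. Every planned RCC must come from the five newly diagnosed patients. An expectation of five malignant cases would need all of those five to be RCC, whereas the protocol expects 75% to 80%.

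The shortfall cannot be prevented when a newly diagnosed patient enters, because that patient is scanned before biopsy. Nor does the article describe a later correction. Arm allocation follows the availability of kits, deuterated drink and scanner. Replacement is limited to withdrawal or failure to complete a scan. A participant is evaluable after one scan, whatever the pathology.

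The error runs in one direction: the oncocytic group is over-filled and the RCC group is short. The benign-malignant contrast is the ultimate aim in every arm, and the results are meant to inform a larger study, so the stated group sizes should be ones the scheme can be expected to produce.

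**Working it through.** **Inputs, all from the protocol article**

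- Patients per arm: 10, in three arms (Participant selection).
- Newly diagnosed: half, so 5 per arm (same section).
- RCC rate among them: p = 0.75 to 0.80 (same section).
- Known oncocytic: the other 5, expected RCC 0 (same section).
- Aim: at least 4 RCC and at least 4 oncocytic per arm (same section).
- Stated composition: 5 benign and 5 malignant per arm, 15 and 15 overall (sample size section).

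**Step 1. The stated figure.** 30 ÷ 3 = 10 per arm and 15 ÷ 3 = 5 of each type per arm. The 5 and 5 follows from dividing the totals equally. It does not use the RCC rate.

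**Step 2. Expected composition under the recruitment scheme.**

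- RCC per arm = 5p = 3.75 to 4.00.
- Non-RCC per arm = 10 − 5p = 6.25 to 6.00.
- Over three arms: RCC 11.25 to 12, non-RCC 18.75 to 18. The stated 15 malignant is 3 to 3.75 too high.

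**Step 3. Chance of reaching each target.** Let X be the number of RCCs among the five, X ~ Binomial(5, p).

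| Quantity | p = 0.75 | p = 0.80 |
|---|---|---|
| P(X = 5) = p⁵ | 0.237 | 0.328 |
| P(X = 4) = 5p⁴(1 − p) | 0.396 | 0.410 |
| P(X ≥ 4) | 0.633 | 0.737 |
| P(X < 4) | 0.367 | 0.263 |
| All three arms ≥ 4 (cube) | 0.253 | 0.401 |
| All three arms = 5 (cube) | 0.013 | 0.035 |

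The last two rows treat the arms as independent. Patients who have a second scan with another technique count in both arms, so those rows are approximate.

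**Step 4. Cost in precision.** With equal variances in the two groups (an assumption), the standard error of a difference is proportional to √(1/n₁ + 1/n₂).

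- 5:5 gives √0.400 = 0.632.
- 6:4 gives √0.417 = 0.645, which is 2% larger.
- 7:3 gives √0.476 = 0.690, which is 9% larger.
- Averaged over Binomial(5, p), leaving out the negligible case of no RCC, the increase over 5:5 is 4% (p = 0.80) to 6% (p = 0.75).

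**Step 5. Alternative source splits with 10 per arm.**

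| Newly diagnosed : surveillance | Expected RCC | P(≥ 4 RCC) | Both minimums met |
|---|---|---|---|
| 5 : 5 | 3.75–4.00 | 63%–74% | 63%–74% |
| 6 : 4 | 4.5–4.8 | 83%–90% | 83%–90% |
| 7 : 3 | 5.25–5.6 | 93%–97% | 76%–80% |

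With 5:5 or 6:4 the surveillance patients alone meet the oncocytic minimum. With 7:3 at least one newly diagnosed patient must also be non-RCC, so both minimums are met with probability P(4 ≤ X ≤ 6) for X ~ Binomial(7, p): 0.929 − 0.133 = 0.796 at p = 0.75, and 0.967 − 0.210 = 0.757 at p = 0.80. This counts every non-RCC as oncocytic, which favours 7:3. Of the three splits, 6:4 does best on both minimums.

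**The case against.** The strongest reply is that this is a feasibility study. Its primary objective is technical development, no diagnostic accuracy analysis is foreseen, the sizes are called pragmatic, 30 is an upper limit, and four-and-four is introduced as an aim. An arm with three RCCs still serves description, and at least three are reached with probability 90% to 94%. The average loss of precision is 4% to 6%, and the 6:4 split still averages 2% to 3%. All of this stands, and it limits the weight of the point. It does not make the stated 5 and 5 agree with the stated rate.

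A second reply is that the binomial model is rigid. The chief investigator allocates patients over a long recruitment period, so earlier pathology could inform later enrolment, and Table 1 admits confirmed malignant masses. That is possible, but the recruitment scheme as written uses neither route, and the allocation basis it gives is availability.

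Some stronger readings are tempting but not supported:

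- A reader might infer that five malignant cases per arm are impossible. They are not: an arm reaches five in 24% to 33% of cases.
- A reader might infer that four-and-four contradicts five-and-five. It does not: the first is a floor, and 5:5 satisfies it. The conflict is between 5:5 and the 75% to 80% rate.
- A reader might infer lost statistical power. The article plans descriptive statistics and states no test or interval for this contrast.
- A reader might add that biopsies "are non-diagnostic in up to 20% of cases" and take the chance of four confirmed RCCs down to 34% to 41% per arm. That is a worst case: it treats an upper bound from the background section as the actual rate and assumes no diagnosis at surgery, which the protocol allows.

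**Conclusion.** The point holds as an inconsistency between two sections, with a modest practical consequence. The stated 15 malignant participants should read about 11 to 12 under the current scheme. The shortfall is one to one and a quarter RCCs per arm on average, and roughly one arm in four to one in three falls below the plan's own minimum. The claim that the scheme secures balance is too strong.

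The figures assume exactly five newly diagnosed patients per arm, independent diagnoses, no RCC in the known oncocytic half, and RCC and oncocytic neoplasm standing for malignant and benign. A reclassification at surgery could add an RCC, but the plan does not count on one. The per-arm figures do not depend on independence between arms. Where a patient counts in two arms, the totals count arm places rather than people.

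**What to change.** **Minimum change.** Reconcile the two sections. If the half-and-half source split is kept, restate the expected totals as about 11 to 12 RCC and 18 to 19 non-RCC, and replace the statement that balance is assured with one that gives the expected split. Keep at least four of each per arm as the single working target.

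**Preferred change.** Keep ten per arm but recruit six newly diagnosed and four surveillance patients. The four surveillance patients still meet the oncocytic minimum. Expected RCCs become 4.5 to 4.8 per arm, or 13.5 to 14.4 overall (15.6 to 16.5 non-RCC), and the totals should be restated to match. The chance of at least four RCCs rises to 83% to 90% per arm. For all three arms it is about 57% to 73%, so the change reduces the problem without removing it.

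**Cost.** Total size does not change. Three more newly diagnosed and three fewer surveillance patients are needed across the study. Both sections need new text, in a short amendment that passes through the sponsor and the REC/HRA. Whether and when to top up an arm with biopsy-proven RCC, which Table 1 would admit, is for the sponsor to decide; neither change depends on it.
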